# Treatment of adolescents with depression: the effect of transference interventions in a randomized controlled study of dynamic psychotherapy

**DOI:** 10.1186/1745-6215-13-159

**Published:** 2012-09-06

**Keywords:** Psychodynamic, Transference, Randomized trial, Adolescent, Depression, Gender

## Abstract

**Background:**

Depression in adolescents seems to be a growing problem that causes mental suffering and prevents young people from joining the workforce. There is also a high risk of relapse during adult life. There is emerging evidence for the effect of psychodynamic psychotherapy in adolescents. In-session relational intervention (that is, transference intervention) is a key component of psychodynamic psychotherapy. However, whether depressed adolescents profit most from psychodynamic psychotherapy with or without transference interventions has not been stated.

**Object:**

The effect of transference interventions in depressed adolescents and the moderator moderating effect of quality of object relations, personality disorder and gender will be explored.

**Methods and study design:**

The First Experimental Study of Transference Work–In Teenagers (FEST–IT) will be a randomized clinical trial with a dismantling design. The study is aimed to explore the effects of transference work in psychodynamic psychotherapy for adolescents with depression. One hundred patients ages 16 to 18 years old will be randomized to one of two treatment groups, in both of which general psychodynamic techniques will be used. The patients will be treated over 28 weeks with either a moderate level of transference intervention or no transference intervention. Follow-up will be at 1 year after treatment termination. The outcome measures will be the Psychodynamic Functioning Scales (PFS), Inventory of Interpersonal Problems–Circumplex Version (IIP-C), Global Assessment of Functioning (GAF), and the total mean score of Symptom Checklist–90 (Global Severity Index; GSI), Beck Depression Inventory (BDI), and Montgomery Åsberg Rating Scale (MADRS). The quality of adolescents’ relationships will be a central focus of the study, and the Adolescent Relationship Scales (ARS) and Differentiation–Relatedness Scale (DRS) will also be used. Change will be assessed using linear-mixed models. Gender personality disorder (PD) and quality of object relations (QOR) will be the preselected putative moderators.

**Discussion:**

The object of this clinical trial is to explore the effect of transference interventions in psychodynamic psychotherapy in adolescents with a major depressive disorder. Using a randomized and dismantling design, we hope that the study will add more specific knowledge to the evidence base.

**Trial registration:**

ClinicalTrials.gov Identifier: NCT01531101

First Experimental Study of Transference work Work–In Teenagers (FEST-IT)

## Background

The number of young people (ages 16 to 24 years old) disabled by psychiatric disorders has tripled during the past 30 years. Among this group, 25% have been unable to work because of anxiety, depression, personality disorders or behavioral disorders. Young women especially have shown a significant increase in psychiatric symptoms, particularly depression and anxiety. Studies indicate that young women more than men of the same age and older women suffer from psychological distress and that girls present higher rates of depression than boys, whereas boys present higher rates of mania
[1-4].

In addition to the mental suffering that these disorders cause, they carry a great risk of becoming chronic without adequate treatment, which may prevent individuals who have them from joining the workforce. The World Health Organization uses a measure, “years lost due to disability” (YLD; number of affected × seriousness of the disease × average duration of illness), to calculate the burden of different diseases on populations. Globally, depression has the highest YLD score
[5,6].

Common treatment given to adults with depression is antidepressant medication or psychotherapy of short to intermediate duration. The effects of antidepressants might be questionable
[7,8]. In the Treatment for Adolescents with Depression Study (TADS), adolescents with moderate to severe depression were observed to improve more with antidepressants and from a combination of antidepressants and cognitive-behavior therapy (CBT) than from CBT
[9]. The effects of antidepressants on adolescents have not been explored to the same extent as they have for adults, and the results are contradictory. Antidepressant medication is recommended for adolescents in the USA
[10], for example, but the UK NICE guidelines
[11] do not advise antidepressant medication for a young person with moderate to severe depression, except in combination with a concurrent psychological therapy. According to a recent review, counseling and psychotherapy together is the treatment of choice in adolescents with major depressive disorder (MDD). However, in severe cases, antidepressants might be used for depression in adolescents in combination with psychotherapy
[12].

In adolescent psychotherapy, as well as in adult psychotherapy, psychodynamic theory is one of the main theoretical approaches and is a treatment model based on principles described in the literature over several decades. Psychodynamics-based therapies comprise a wide spectrum of theoretical approaches; for example, mentalization, attachment, self-psychology object relations, and relational aspects
[13-18]. *Transference* is a key concept in dynamic psychotherapy, and analysis of the transference distinguishes this treatment from other treatments. There is probably an array of active ingredients in the therapeutic action of psychotherapy with adolescents. Three of them might be analysis of transference, personality traits and gender.

*Analysis of transference* (transference work) is thought to be a fundamental technique in dynamic psychotherapy
[19,20] with adults as well as with adolescents. The ongoing interaction between patient and psychotherapist is heavily influenced by the patient’s past relationships and affective experiences. A focus on the themes and conflicts that arise in the therapeutic relationship will therefore have immediate affective resonance and illuminate the nature of problems in the patient’s relationships outside therapy
[21-24]. There are only two experimental and controlled studies in adults on the effect of transference work
[25-27]. No experimental study has explored the effect of transference work in adolescents and identified for whom it works.

*Personality traits* influence the effect of psychotherapy
[28]. However, the impact of difficulties in relational functioning and/or personality disorder on the effect of psychodynamic psychotherapy in adolescents has not been empirically explored
[29].

*Gender* has not been found to be a general predictor in psychotherapy
[28]. Few studies of adult patients
[30-35] have explored gender as a moderator
[36] of individual psychotherapy, which means testing whether female and male patients responded differently to different psychotherapy treatments. Ogrodniczuk *et al*.
[31], Ulberg *et al*.
[32,33], Frank *et al*.
[34] and Barber *et al*.
[35] found that gender moderates the effect of psychotherapy. The findings from research on the effect of gender in children and young people seem contradictory
[37]. To the best of our knowledge, no experimental study has explored differences in response to transference interventions in dynamic psychotherapy between teenage girls and boys.

The field of psychotherapy research has made great advances in the past few decades. More than 1,500 studies have explored the effect of psychotherapy with children and adolescents
[38]. However, randomized studies of the effect of dynamic psychotherapy in adolescents are few
[39]. In a review of randomized controlled trials of CBT and psychodynamic psychotherapy, Thomas and colleagues did not find that studies differed significantly in quality
[40]. However, one putative difference between CBT and psychodynamic psychotherapy might be that dynamic psychotherapy can have a long-term effect in adolescents. That is, the effect of treatment continues after termination in adults as well as in children and adolescents
[41]. This is in contrast to some studies of CBT which did not give any evidence of a possible “sleeper effect”
[42]. Meta-analytic reviews have provided support for the effectiveness of psychodynamic psychotherapy approaches to the treatment of mental disorders
[43]. A strong evidence base for psychodynamic treatment of adolescents with depression is emerging
[41,44].

Establishing that psychotherapy does have an effect does not, however, tell us much about *how, why* and *for whom* psychotherapy works. Therapists need to adjust and tailor their treatment approaches to the individual patient. Taking into account that individual psychotherapy is frequently the treatment of choice and is supposed to be beneficial for teenagers with depression, a research challenge is to further explore and establish empirically which techniques are critical to include for patients with different characteristics
[45].

A randomized clinical trial (RCT) is a study in which an intervention is applied to diagnosed cases and analyzed against a comparison condition to determine the degree of change associated with treatment
[46]. In a randomized controlled study, the included patients are randomized to a study treatment condition or to a different treatment condition or placebo. The response in a treatment group is compared to the response in a control condition. The efficacy of a treatment might thus be determined. Patients and evaluators should be blinded to treatment group. Efficacy studies emphasize the internal validity by (1) controlling the types of patients included in the study, (2) using manuals to standardize the treatment, (3) training the therapists prior to the study, (4) supervising the therapists during treatment, (5) monitoring the technique adherence and the “dose” of the therapy, (6) assigning participants randomly to treatments, and (7) selecting the primary outcome measures before the study begins
[47].

Borkovec and Sibrava
[48] stated that even the RCT method applied in psychotherapy research might ignore what specific therapist behavior causes the change in the patient during and after therapy. They maintained that psychotherapy studies mostly compare therapy modes that differ in a number of ways. Therefore, RCTs often do not generate significant basic knowledge.

Borkovec and Sibrava’s advice is to focus on identification of putative specific techniques that cause patient improvement. Studies should investigate treatment conditions that differ in only one component. Dismantling or component control designs contrast the complete therapy (for example, dynamic psychotherapy with transference interventions) with the same therapy with experimentally manipulated differences solely in one dimension (for example, dynamic psychotherapy without transference interventions). If the patient expectations and the quality of the patient–therapist relationship in both conditions are equal, therapist effects are minimized, and the quality with which interventions are given is equal in both groups, then the study offers the best possibility of detecting causal relationships between the specific technique and outcome.

There is a need for experimental studies. To provide this specific knowledge about adolescents, a RCT with a dismantling design will probably be the most suitable method. The present study is planned to be basic research on psychodynamic psychotherapy. With the intention being to contribute to the evidence base, the study will be an adjusted replication in adolescents with MDD, of the First Experimental Study of Transference–Interpretations. The Manual for Short-Term Psychoanalytic Therapy (STPP) from the Improving Mood with Psychoanalytic and Cognitive Therapies (IMPACT)–Study
[49] and some of the measures in the Erica Process and Outcome Study (EPOS)
[37] will be part of the assessment battery in FEST–IT.

### Related studies

#### First Experimental Study of Transference–Interpretations

The First Experimental Study of Transference–Interpretations (FEST)
[27] is a RCT designed to explore specific long-term effects of transference work in time-limited dynamic psychotherapy in adults. Regular patients from general practice, private specialist practices and psychiatric outpatient departments were referred to the study therapists and assessed for eligibility. Inclusion criteria were liberal. One hundred patients were randomized to two different dynamic psychotherapies. Both treatments used general psychodynamic principles. One treatment avoided an interpretive focus on the ongoing patient–therapist interaction (comparison group). The other treatment used material from the patient–therapist interaction as the most important vehicle for clarifications, confrontations and interpretations (transference group).

In FEST, no significant differences between the two groups with regard to baseline characteristics could be detected. Treatment integrity was excellent
[26]. Only use of transference work was significantly different between the two treatments. The two primary outcome measures were the Psychodynamic Functioning Scales (PFS) (clinician-rated)
[25,26,50,51] and the Inventory of Interpersonal Problems (IIP–C)
[52]. The two secondary outcome measures were the Global Assessment of Functioning Scale (GAS) and the Symptom Checklist-90-R (SCL-90)
[53].

The Quality of Object Relation Scale (QOR), a measure of difficulties in relational functioning
[54], was an important moderator of the effect of transference interventions
[26,27]. Patients with the most problematic relationships with other people profited most from dynamic psychotherapy with transference interventions. Gender was also found to be a moderator
[32,33]: Women experienced a significantly better treatment effect of transference work than men.

#### Improving Mood with Psychoanalytic and Cognitive Therapies study

The IMPACT study is an ongoing, large-scale RCT of depressed adolescents in the United Kingdom which will explore whether CBT or STPP is superior in reducing relapse compared with specialist clinical care in adolescents with unipolar depression. One hundred eighty patients will be randomized to each arm. The psychodynamic/psychoanalytic arm of the study is STPP. Patients will be assessed at pretreatment and at 6, 12, 36, 52 and 86 weeks after the beginning of therapy
[49].

Erica Process and Outcome StudyEPOS
[37] is a naturalistic, multicenter, pre-post study evaluating children’s functioning after psychotherapy. Quantitative and qualitative methods are used to describe factors underlying change.

## Methods/design

### Overview

The First Experimental Study on Transference Work–In Teenagers (FEST–IT) will be a RCT designed to explore effects of transference work in dynamic psychotherapy in adolescents with MDD. The design of the study is a so-called dismantling design in which a single component is added and/or varied to an existent treatment method (psychodynamic psychotherapy). Thus, the efficacy of a specific technique (transference interventions) can be identified.

### Aims

The primary hypothesis is that the transference group will have a more favorable course than the comparison group over time (that is, a significant improvement on the Psychodynamic Functioning Scales (PFS) and Inventory of Interpersonal Problems–Circumplex Version (IIP-C) and the measured depression by Mini International Neuropsychiatric Interview (M.I.N.I.), Beck Depression Inventory (BDI) and Montgomery Åsberg Rating Scale (MADRS) during the whole study period). The second hypothesis is that patients with a history of low QOR scale score and/or lacking personality disorders benefit more from therapy with transference work than from therapy without it. The third hypothesis is that female adolescents have better treatment effect of transference work than male adolescents do.

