### Planned investigations

FEST–IT will be a randomized trial that compares short-term psychodynamic psychotherapy with and without transference interpretation to reduce relapse in adolescents with DSM-IV-defined MDD. The patients will be randomly allocated to STPP with or without transference interventions. This is a dismantling design in which a single component is added and/or varied to an existing treatment approach. The therapy is manualized. Outcomes will be assessed at planned follow-up points by outcome evaluators unaware of the treatment allocation. The therapists will be psychodynamically trained therapists who will undergo a 1-year training program succeeded by peer supervision in groups. This will help maintain the quality of the therapies. The therapies will be audiotaped to evaluate treatment adherence.

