### Sample size and power

On the basis of standard posttest comparison of the two groups, 100 patients in this study will be enough to reveal a moderate effect size (0.55), with a significance level of 0.05 and a power of 0.80
[74]. In this study, an effect size (ES) of 0.55 equals 3.3 steps on the GAF scale, since the standard deviation across groups at posttreatment is 6. By using a pre-post treatment design, the power will increase. Adding data from 1-year follow-up will increase the power to detect differences even more. An α level of 0.10 has been decided on *a priori* for the moderator analyses and the subgroup analyses in this study to offset the risk of type II errors
[74].

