## Discussion

Depression in adolescents might relapse, and treating and preventing further symptoms can help young people find their way into adult relationships and into the workforce. To guide therapists in which therapy works for patients with different characteristics, there is a need for more studies to investigate the effect of psychotherapy.

According to Borkovec and Costello
[79], the study will have a RCT dismantling design. Differences in psychodynamic psychotherapy with and without transference interventions will be explored. Thus solely one technique, the transference interventions, will be experimentally manipulated. The present design will fulfill RCT requirements: Treatment will be based on clear descriptions from a manual. Power calculation will be made. Primary and secondary hypotheses will be defined. The patients will be unaware of which treatment group they have been assigned to. Real patients will be randomized to therapy (treatment and comparison group) and treated by specially trained therapists. The patients will be diagnosed on the basis of formal interviews (M.I.N.I. and SIDP-IV). Assessments will be conducted at three time points with the primary outcome variables using the PFS-5 and the secondary outcome measure using GAF. Assessments will also be undertaken at four time points using the primary outcome measure IIP–C and the secondary outcome measure GSI. Evaluators will be blinded into which treatment group patients were placed. Reliability will be tested between the raters on the GAF, PFS–5 and QOR − 2. Moderators specified in advance (QOR–2, PD and gender). The present study aims to explore the effect of transference interventions in psychodynamic psychotherapy, and we hope it will add more knowledge to the evidence base for treatment of adolescents with major depression.

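### The Aims and the Discussion name different primary measures, and a relapse aim has no outcome, so what would confirm the primary hypothesis is ambiguous

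*Protocol article*

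**What the plan says.** All places are in the protocol article.

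- **Aims.** The primary hypothesis is that the transference group has the better course, spelled out as "a significant improvement on the Psychodynamic Functioning Scales (PFS) and Inventory of Interpersonal Problems–Circumplex Version (IIP-C" and, joined by a further *and*, also "the measured depression by Mini International Neuropsychiatric Interview (M.I.N.I.), Beck Depression Inventory (BDI) and Montgomery Åsberg Rating Scale (MADRS) during the whole study period". That makes five measures.
- **Discussion.** Two sentences attach ranks to measures: "Assessments will be conducted at three time points with the primary outcome variables using the PFS-5 and the secondary outcome measure using GAF", and then four assessments "using the primary outcome measure IIP–C and the secondary outcome measure GSI". BDI, MADRS and M.I.N.I. receive no rank.
- **Abstract, Methods and study design.** PFS, IIP-C, GAF, GSI, BDI and MADRS are listed as outcomes without ranking.
- **Planned investigations.** The trial compares the therapy "with and without transference interpretation to reduce relapse in adolescents with DSM-IV-defined MDD". No section defines remission or relapse or gives an analysis of it.
- **Statistical analysis plan.** One linear mixed model equation, with a generic outcome on the left-hand side, is assigned to the primary hypothesis.
- **Sample size and power.** The calculation says "100 patients in this study will be enough to reveal a moderate effect size (0.55"), qualifies this "with a significance level of 0.05 and a power of 0.80", and adds that "an effect size (ES) of 0.55 equals 3.3 steps on the GAF scale, since the standard deviation across groups at posttreatment is 6". GAF is in neither version of the primary set.

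**The concern.** A primary hypothesis stated as a result on named measures should use the measures that the protocol labels primary. Here three of the five named in the Aims are missing from the measures labelled primary in the Discussion. One investigator could report the hypothesis as confirmed on PFS-5 and IIP-C while another, with the same data, reports it as not confirmed because BDI or MADRS did not separate the arms.

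The choice also changes the kind of evidence. PFS is scored by two blinded raters. MADRS is completed by the therapist up to posttreatment (Table 1), and the therapist knows the arm (Recruitment and baseline procedures). The five-measure set therefore brings a largely unblinded rating into the primary claim.

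Two further items do not fit together. The relapse aim has no outcome behind it. And M.I.N.I. depression is a yes/no diagnosis that every patient must have to be randomized, so it has no variation at baseline and only two later readings. A linear mixed model with a time trend and normal residuals is a poor description of such data.

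**Working it through.** **1. The passages side by side**

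| Measure | Aims (primary hypothesis) | Discussion (rank) | Abstract |
|---|---|---|---|
| PFS / PFS-5 | yes | primary | listed |
| IIP-C | yes | primary | listed |
| M.I.N.I. depression | yes | none | not listed |
| BDI | yes | none | listed |
| MADRS | yes | none | listed |
| GAF | no | secondary | listed |
| GSI | no | secondary | listed |
| Relapse | no | none | not listed |

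The number of primary measures is k = 5 by the Aims and k = 2 by the Discussion labels.

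**2. The stated power**

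Inputs from Sample size and power: effect 0.55 SD (3.3 / 6 = 0.55), 100 patients, alpha 0.05. Assumed: 50 per arm (therapists treat equal numbers in each mode) and a two-sided test (sidedness is not stated).

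Expected z = 0.55 × √(50/2) = 0.55 × 5 = 2.75. Power = Φ(2.75 − 1.96) = Φ(0.79) = 0.785. This reproduces the stated 0.80 to within two percentage points.

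**3. If any one measure suffices**

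- Both directions, independent measures: 1 − 0.95² = 0.0975 and 1 − 0.95⁵ = 0.226.
- Only results favouring transference work, independent: 1 − 0.975² = 0.049 and 1 − 0.975⁵ = 0.119, against 0.025 for one test.

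The measures will be correlated, but the article gives no correlation. The range below takes k equally correlated normal test statistics.

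| Assumed correlation | k=2, both directions | k=2, favourable | k=5, both directions | k=5, favourable |
|---|---|---|---|---|
| 0 | 9.8% | 4.9% | 22.6% | 11.9% |
| 0.5 | 9.1% | 4.5% | 18.3% | 9.2% |
| 0.9 | 7.0% | 3.5% | 10.2% | 5.1% |

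**4. If all measures must be significant**

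The favourable error is at most 2.5%, so nothing is inflated. Power needs a further assumption, that the effect is 0.55 on every measure. With independence it is 0.785² = 0.617 and 0.785⁵ = 0.299.

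| Assumed correlation | k=2 | k=5 |
|---|---|---|
| 0 | 62% | 30% |
| 0.5 | 67% | 49% |
| 0.9 | 73% | 67% |

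All of these are on the simple posttest basis used in the article's own calculation. For k = 5 they treat M.I.N.I. status as if it yielded a test of the same strength as the scales.

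**The case against.** The strongest case on the other side has five parts.

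- **Inflated error is not established.** The Aims join the measures with *and*. Read literally, all must improve, which costs power and inflates nothing. Inflation follows only from an any-of rule, or from choosing the deciding measure after seeing the data, and the article states neither. This stands. A reader might infer that the trial's type I error is inflated; the document does not support that. The hypothesis is also directional, so the two-directional figures overstate the chance of a false claim for transference work by about a factor of two.
- **A combination rule may sit in the SAP.** This stands. The 0.05 level appears only in the power statement, and the absence of a multiplicity rule from a condensed article is no finding. The contradiction between sections does not depend on the SAP.
- **There is a time target.** A reader might infer that no primary time point means no estimand. The Aims speak of the course over the whole study period, and the analysis section matches this with a time × treatment term on all data. That is a legitimate longitudinal contrast and needs no single visit.
- **Relapse could be derived.** M.I.N.I. is repeated at posttreatment and at 1 year, so relevant data are collected. This stands. What is missing is a definition.
- **The Discussion may not be an exhaustive ranking.** Its sentences group measures by number of assessments (three or four), and BDI and MADRS have five in Table 1. This softens the point to an ambiguity, but three measures in the primary hypothesis still carry no primary label anywhere.

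The article also says that pre-post and follow-up data will raise power above the posttest figure, so the power values in the working are not forecasts for the planned model.

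**Conclusion.** The inconsistency is real and lies in the current text. The Aims give five measures for the primary hypothesis, the Discussion labels two, and Planned investigations adds a relapse aim without an outcome. M.I.N.I. depression does not suit the model assigned to the primary hypothesis. The criterion for confirming that hypothesis is therefore ambiguous, and this needs correcting before analysis.

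The size depends on how the ambiguity is resolved. An any-of reading would roughly double the favourable error with two measures at low correlation, and multiply it by two to nearly five with five measures. An all-of reading keeps the error but leaves power below the stated 0.80 at every correlation examined, by a little with two strongly correlated measures and by 50 points with five independent ones. These figures rest on assumed correlations of 0 to 0.9 and, for power, on a common effect of 0.55 and 50 per arm. The stated 0.80 is itself expressed on GAF, which the Discussion calls secondary.

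The documents do not show that error is inflated, and they do not require a single primary outcome: the Background's list of features of efficacy studies speaks of primary outcome measures in the plural.

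**What to change.** 1. State one primary set in the Abstract, Aims and Discussion. The simplest choice is PFS-5 and IIP-C, which already carry the label. Keep the longitudinal time × treatment contrast. A single primary measure is another valid option.
2. Say how the two are combined, for example by Holm or in a fixed sequence.
3. List GAF, GSI, BDI, MADRS and M.I.N.I. depression as secondary.
4. Analyse M.I.N.I. depression status at posttreatment and 1 year with a model for binary data.
5. Either delete the relapse phrase from Planned investigations or define relapse from the M.I.N.I. data already collected.

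The cost is protocol wording and a matching registry update; the article describes the study as ongoing. The downside is fewer routes to a primary claim. A fixed sequence leaves the first measure at 0.05. Under Holm the first step is at 0.05 / 2 = 0.025, where power for one measure on the posttest basis is Φ(2.75 − 2.24) = 0.69; bringing that to 80% would take 126 patients.
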